| Mucositis/
Stomatitis
(symptomatic)                                  | Minimal
symptoms,
normal diet                                              | Symptomatic but
can eat and
swallow modified
diet                                                                       | Symptomatic and
unable to adequately
aliment or hydrate
orally                                                                                                  | Symptoms associated
with life-threatening
consequences                              |
| Nausea                                                                       | Loss of appetite
without alteration
in eating habits                       | Oral intake
decreased without
significant weight
loss, dehydration or
malnutrition; IV
fluids indicated
<24hrs | Inadequate oral
caloric or fluid intake;
IV fluids, tube
feedings or total
parenteral nutrition
(TPN) indicated ≥24
hrs                                | Life-threatening
consequences                                                          |
| Vomiting                                                                     | 1 episode in 24
hours                                                         | 2-5 episodes in 24
hours; IV fluids
indicated < 24hours                                                                    | ≥ 6 episodes in 24
hours; IV fluids, or
TPN indicated ≥
24hrs                                                                                                   | Life- threatening
consequences                                                         |
| Perforation GI
(oesophagus,
Stomach,
duodenum,
ileum, colon) | Asymptomatic,
radiographic
finding only                                    | Medical
intervention
indicated, IV fluids
indicated < 24hrs                                                             | IV fluids, tube
feedings, or TPN
indicated ≥ 24hrs;
operative intervention
indicated                                                                         | Life-threatening
consequences                                                          |
| Haemorrhage, GI                                                              | Mild, intervention
(other than iron
supplements) not
indicated          | Symptomatic and
medical
intervention or
minor cauterization
indicated                                                | Transfusion,
interventional
radiological,
endoscopic or
operative intervention
indicated; radiation
therapy (i.e.,
haemostasis of
bleeding site) | Life- threatening
consequences; major
urgent intervention
indicated              |
| ALT / AST                                                                    | >ULN – 2.5 x
ULN                                                              | >2.5 – 5.0 x ULN                                                                                                                 | >5.0 – 20.0 x ULN                                                                                                                                                        | >20.0 x ULN                                                                               |
| Bilirubin                                                                    | >ULN – 1.5 x
ULN                                                              | >1.5 – 3.0 x ULN                                                                                                                 | >3.0 – 10.0 x ULN                                                                                                                                                        | >10.0 x ULN                                                                               |
| Hypocalcemia                                                                 | <LLN – 2.0
mmol/L                                                             | <2.0 – 1.75 mmol/L                                                                                                               | <1.75 – 1.5 mmol/L                                                                                                                                                       | <1.5 mmol/L                                                                               |
| Creatinine                                                                   | >ULN-1.5 x ULN                                                                   | >1.5-3.0 x ULN                                                                                                                   | >3.0-6.0 x ULN                                                                                                                                                           | >6.0 x ULN                                                                                |
| Glomerular
Filtration Rate                                               | <75-50% LLN                                                                      | <50-25% LLN                                                                                                                      | <25% LLN, chronic
dialysis not indicated                                                                                                                              | Chronic dialysis or renal
transplant indicated                                         |
| Hypomagnesia                                                                 | <LLN – 0.5
mmol/L                                                             | <0.5 – 0.4 mmol/L                                                                                                                | <0.4 – 0.3mmol/L                                                                                                                                                         | <0.3 mmol/L                                                                               |
| Proteinuria                                                                  | 1+ or 0.15-
1.0g.24hrs                                                        | 2+ to 3+ or >1.0 -
3.5g/24hrs                                                                                                 | 4+ or >3.5g/24hr                                                                                                                                                         | Nephrotic syndrome                                                                        |
| Hyperuricemia                                                                | >ULN – 10mg/dL
≥0.59 mmol/L
without
physiologic
consequences         |                                                                                                                                  | >ULN – 10mg/dL
≥0.59 mmol/L with
physiologic
consequences                                                                                                       | >10mg/dL
≥0.59 mmol/L                                                                  |
| Dizziness                                                                    | With head
movements or
nystagmus only;
not interfering
with function | Interfering with
function, but not
interfering with ADL                                                                    | Interfering with ADL                                                                                                                                                     | Disabling                                                                                 |

|                                       |                                                                                |                                                                                                                                                                                              |                                                                                                                                                                                                                                                                    |                                                                                              |
|---------------------------------------|--------------------------------------------------------------------------------|----------------------------------------------------------------------------------------------------------------------------------------------------------------------------------------------|--------------------------------------------------------------------------------------------------------------------------------------------------------------------------------------------------------------------------------------------------------------------|----------------------------------------------------------------------------------------------|
| Bronchospasm                   | Asymptomatic                                                                   | Symptomatic not with interfering function                                                                                                                                                    | Symptomatic with interfering function                                                                                                                                                                                                                              | Life-threatening                                                                             |
| Cough                          | Symptomatic, non-narcotic medication only indicated                            | Symptomatic and narcotic medication indicated                                                                                                                                                | Symptomatic and significantly interfering with sleep or ADL                                                                                                                                                                                                        |                                                                                              |
| Dyspnea                        | Dyspnea on exertion but can walk 1 flight of stairs without stopping           | Dyspnea on exertion but unable to walk 1 flight of stairs or 1 city block (0.1km) without stopping                                                                                           | Dyspnea with ADL                                                                                                                                                                                                                                                   | Dyspnea at rest; intubation/ventilator indicated                                             |
| Cytokine release syndrome      | Mild reaction; infusion interruption not indicated; intervention not indicated | Requires therapy of infusion interruption but responds promptly to symptomatic treatment (e.g. antihistamines, NSAIDS, narcotics, IV fluids); prophylactic medications indicated for ≥24 hrs | Prolonged (i.e. not rapidly responsive to symptomatic medication and/or brief interruption of infusion); recurrence of symptoms following initial improvement; hospitalization indicate for other clinical sequelae (e.g. renal impairment, pulmonary infiltrates) | Life-threatening; pressor or ventilatory support indicated                                   |
| Tumour flare                   | Mild pain not interfering with function                                        | Moderate pain; pain or analgesics interfering with function, but not interfering with ADL                                                                                                    | Severe pain; pain of analgesics interfering with function and interfering with ADL                                                                                                                                                                                 | Disabling                                                                                    |
| Arterial vessel injury         | Asymptomatic diagnostic finding, intervention not indicated                    | Symptomatic (e.g. claudication) not interfering with ADL, repair or revision not indicated                                                                                                   | Symptomatic interfering with ADL; repair or revision indicated                                                                                                                                                                                                     | Life-threatening; disabling; evidence of end organ damage (e.g. CVA, MI, organ or limb loss) |
| Thrombosis/ thrombus/ embolism | -                                                                              | Deep vein thrombosis or cardiac thrombosis; intervention (e.g., anticoagulation, lysis, filter, invasive procedure) not indicated                                                            | Deep vein thrombosis or cardiac thrombosis; intervention (e.g., anticoagulation, lysis, filter, invasive procedure) not indicated                                                                                                                                  | Embolic event including pulmonary embolism or life threatening thrombus                      |

**NB: These are selected categories. For full list see <http://ctep.cancer.gov/reporting/ctc.html>**

For all cases where applicable grade 5 is death

## APPENDIX XII

### RTOG/EORTC LATE RADIATION MORBIDITY SCORING SCHEMA

|                     | 0    | 1                                                                                                            | 2                                                                                                                           | 3                                                                                                                                        | 4                                                                             |
|---------------------|------|--------------------------------------------------------------------------------------------------------------|-----------------------------------------------------------------------------------------------------------------------------|------------------------------------------------------------------------------------------------------------------------------------------|-------------------------------------------------------------------------------|
| Skin                | None | Slight atrophy
Pigmentation change
Some hair loss                                                      | Patch atrophy;
Moderate telangiectasia;
Total hair loss                                                               | Marked atrophy;
Gross telangiectasia                                                                                                  | Ulceration                                                                    |
| Subcutaneous Tissue | None | Slight induration (fibrosis) and loss of subcutaneous fat                                                    | Moderate fibrosis but asymptomatic
Slight field contracture <10% linear reduction                                        | Severe induration and loss of subcutaneous tissue
Filed contracture >10% linear measurement                                           | Necrosis                                                                      |
| Mucous Membrane     | None | Slight atrophy and dryness                                                                                   | Moderate atrophy and telangiectasia
Little mucous                                                                        | Marked atrophy with complete dryness
Severe telangiectasia                                                                            | Ulceration                                                                    |
| Salivary Glands     | None | Slight dryness of mouth
Good response on stimulation                                                      | Moderate dryness of mouth
Poor response on stimulation                                                                   | Complete dryness of mouth
No response on stimulation                                                                                  | Fibrosis                                                                      |
| Spinal Cord         | None | Mild L'Hermite's syndrome                                                                                    | Severe L'Hermite's syndrome                                                                                                 | Objective neurological findings at or below cord level treated                                                                           | Mono, para quadraplegia                                                       |
| Brain               | None | Mild headache
Slight lethargy                                                                             | Moderate headache
Great lethargy                                                                                         | Severe headaches
Severe CNS dysfunction (partial loss of power or dyskinesia)                                                         | Seizures or paralysis
Coma                                                 |
| Eye                 | None | Asymptomatic cataract
Minor corneal ulceration or keratitis                                               | Symptomatic cataract
Moderate corneal ulceration
Minor retinopathy or glaucoma                                        | Severe keratitis
Severe retinopathy or detachment
Severe glaucoma                                                                  | Panopthalmitis/
Blindness                                                  |
| Larynx              | None | Hoarseness
Slight arytenoid edema                                                                         | Moderate arytenoid edema
Chondritis                                                                                      | Severe edema
Severe chondritis                                                                                                        | Necrosis                                                                      |
| Lung                | None | Asymptomatic or mild symptoms (dry cough)
Slight radiographic appearances                                 | Moderate symptomatic fibrosis or pneumonitis (severe cough)
Low grade fever
Patchy radiographic appearances           | Severe symptomatic fibrosis or pneumonitis
Dense radiographic changes                                                                 | Severe respiratory insufficiency
Continuous oxygen
Assisted ventilation |
| Heart               | None | Asymptomatic or mild symptoms
Transient T wave inversion & ST changes
Sinus tachycardia >110 (at rest) | Moderate angina on effort
Mild pericarditis
Normal heart size
Persistent abnormal T wave and ST changes
Low ORS | Severe angina
Pericardial effusion
Constructive pericarditis
Moderate heart failure
Cardiac enlargement
EKG abnormalities | Tamponade
Severe heart failure
Severe constrictive pericarditis         |
| Oesophagus          | None | Mild fibrosis
Slight difficulty in                                                                        | Unable to take solid food normally                                                                                          | Severe fibrosis
Able to swallow                                                                                                       | Necrosis
Perforation                                                       |

|                         |      |                                                                                                       |                                                                                                                 |                                                                                                                                                           |                                                                                |
|-------------------------|------|-------------------------------------------------------------------------------------------------------|-----------------------------------------------------------------------------------------------------------------|-----------------------------------------------------------------------------------------------------------------------------------------------------------|--------------------------------------------------------------------------------|
|                         |      | swallowing solids
No pain on swallowing                                                            | Swallowing semi-solid food
Dilation may be indicated                                                         | only liquids
May have pain on swallowing
Dilation required                                                                                          | Fistula                                                                        |
| Small / Large Intestine | None | Mild diarrhea
Mild cramping
Bowel movement 5 times daily
Slight rectal discharge or bleeding | Moderate diarrhea and colic
Bowel movement >5 times daily
Excessive rectal mucus or intermittent bleeding | Obstruction or bleeding requiring surgery                                                                                                                 | Necrosis/ Perforation
Fistula                                               |
| Liver                   | None | Mild lassitude
Nausea, dyspepsia
Slightly abnormal liver function                               | Moderate symptoms
Some abnormal liver function tests
Serum albumin normal                                 | Disabling hepatic insufficiency
Liver function tests grossly abnormal
Low albumin
Edema or ascites                                               | Necrosis/ Hepatic coma or encephalopathy                                       |
| Kidney                  | None | Slight epithelial atrophy
Minor telangiectasia (microscopic hematuria)                             | Moderate frequency
Generalized telangiectasia
Intermittent macroscopic hematuria                          | Severe frequency and dysuria
Severe generalized telangiectasia (often with petechiae)
Frequent hematuria
Reduction in bladder capacity (<150 cc) | Necrosis/ Contracted bladder (capacity <100 cc)
Severe hemorrhagic cystitis |
| Bladder                 | None | Slight epithelial atrophy
Minor telangiectasia (microscopic hematuria)                             | Moderate frequency
Generalized telangiectasia
Intermittent macroscopic hematuria                          | Severe frequency and dysuria
Severe generalized telangiectasia (often with petechiae)
Frequent hematuria
Reduction in bladder capacity (<150 cc) | Necrosis/ Contracted bladder (capacity <100 cc)
Severe hemorrhagic cystitis |
| Bone                    | None | Asymptomatic
No growth retardation
Reduced bone density                                         | Moderate pain or tenderness
Growth retardation
Irregular bone sclerosis                                   | Severe pain or tenderness
Complete arrest of bone growth
Dense bone sclerosis                                                                       | Necrosis/
Spontaneous fracture                                              |
| Joint                   | None | Mild joint stiffness
Slight limitation of movement                                                 | Moderate stiffness
Intermittent or moderate joint pain
Moderate limitation of movement                    | Severe joint stiffness
Pain with severe limitation of movement                                                                                         | Necrosis/ Complete fixation                                                    |

GUIDELINES from <http://www.rtog.org/members/toxicity/late.html>

All toxicities Grade 3, 4 or 5\* must be verified by the Principal Investigator.

\* ANY TOXICITY WHICH CAUSED DEATH IS GRADED 5.

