#### Nephrotoxicity

Cisplatin produces cumulative nephrotoxicity. If a baseline estimate of renal function using the Cockcroft & Gault formula predicts the GFR to be  $\geq 60\text{mL/min}$  full dose cisplatin should be used. If the estimate is  $<60\text{mL/min}$  an EDTA Creatinine clearance should be performed and the appropriate cisplatin dose used (see table below). In the case of a 25% deterioration in estimated renal function (using the Cockcroft & Gault formula) on pre-treatment blood samples an EDTA Creatinine clearance should be performed and pending this an appropriate dose reduction in cisplatin should be made. The EDTA Creatinine clearance result, when available, takes precedent over estimated GFR for subsequent cisplatin dose calculations.

| GFR (mL/min) Baseline and prior to Day 1 | Action                                                         |
|------------------------------------------|----------------------------------------------------------------|
| $\geq 50\text{mL/min}$                   | Continue full dose                                             |
| 40 - $<50\text{mL/min}$                  | Cisplatin 50% dose
Capecitabine 75% dose                    |
| 30 - $<40\text{mL/min}$                  | Stop cisplatin, use carboplatin AUC 5
Capecitabine 50% dose |
| $< 30\text{mL/min}$                      | Stop cisplatin, use carboplatin AUC 5
Stop capecitabine     |

For a GFR of 50 to  $<60\text{mL/min}$ , a dose reduction of Cisplatin by 50% may be given if local policy.

Consider dose reduction of 5FU in cases of severe renal impairment (i.e.  $\text{GFR} \leq 10\text{mL/min}$ ).

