## 9.2 Organs at Risk

The full extent of the right and left lungs are outlined, this should be done in such a way that the planning system will be able to calculate a combined lung dose volume histogram (DVH).

The spinal cord should be outlined on slices which include or are within 2cm of the PTV in the superior and inferior directions. A Planning Risk Volume (PRV) for the cord is created to account for positioning error, the size of the margin added to the cord being commensurate with the accuracy of treatment delivery expected and as such the tolerance level allowed in portal image verification on treatment.

The whole heart is outlined to the extent of the pericardial sac (if visible). The major blood vessels (superior to the organ) and the inferior vena cava (towards the inferior extent of the heart) are excluded.

The whole liver is outlined if the level of its superior edge overlaps with the level of the inferior extent of the PTV.

Each kidney is outlined separately if the level of its superior edge overlaps with the level of the inferior extent of the PTV.

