| Acne-like rash (see table and diagram on p45 of this of protocol) | Abdominal pain                    | Anaphylactic-like         | Acute gastritis                 |
| Allergic reaction                                                 | Alopecia                          | Neurotoxicity             | Anorexia                        |
| Conjunctivitis                                                    | ALT / AST changes                 | Alopecia                  | Chronic renal damage            |
| Dermatitis                                                        | Anorexia                          | ALT / AST changes         | Diarrhoea                       |
| Dyspnoea                                                          | Bilirubin changes                 | Anorexia                  | Dermatitis                      |
| Dysphagia                                                         | Cardiotoxicity                    | Bilirubin changes         | Dysphagia                       |
| Fatigue                                                           | Cardiac ischaemia / infarction    | Creatinine changes        | Fatigue                         |
| Hypersensitivity                                                  | Central/peripheral nervous system | Fatigue                   | Gastro-intestinal perforation   |
| Hypokalaemia                                                      | Creatinine changes                | Febrile neutropenia       | Gastro-intestinal bleeding      |
| Hypomagnasaemia                                                   | Dermatitis                        | Haemoglobin               | Nausea and vomiting             |
| Oesphagitis                                                       | Diarrhoea                         | Hearing                   | Oesphagitis                     |
| Rash                                                              | Disease                           | Hypocalcaemia             | Radiation dermatitis            |
| Stomatitis                                                        | Fatigue                           | Hypouricemia              | Skin discolouration             |
| Urticaria                                                         | Febrile neutropenia               | Infection with normal ANC | Second malignancy               |

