### 12.2 Outcome measures

#### Stage 1:

The primary outcome measure is treatment failure rate in the research arm. Treatment failure rate will be assessed at 24 weeks (12 weeks after completion of CRT) and is defined as pathologically confirmed (by endoscopic assessment and/or biopsy) residual disease and/or CT scan of thorax and abdomen showing progressive disease according to RECIST criteria.

The secondary outcome measures are: toxicity and feasibility.

- **Toxicity:** will be scored using the NCI CTCAE v3.0 and RTOG acute radiation morbidity scoring criteria (Appendix XII) at baseline, during treatment and at pre-specified time points on follow-up. Serious adverse events will be monitored “real-time” by the Chief Investigator and TMG.
- **Feasibility:** will be measured through the number of protocol dose modifications and delays.

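### Appendix XII grades the Kidney with the Bladder's criteria, so the RTOG/EORTC late scale has no working kidney item

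*Protocol*

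**What the plan says.** Section 12.2, Stage 1, makes toxicity a secondary outcome that "will be scored using the NCI CTCAE v3.0 and RTOG acute radiation morbidity scoring criteria (Appendix XII"). Scoring begins before treatment starts and goes on "during treatment and at pre-specified time points on follow-up". Stage 2 names the same two scales. The schedule in section 5.5 runs toxicity assessment to month 60.

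Appendix XII sets out the RTOG/EORTC late radiation morbidity schema, one row per organ, grades 0 to 4. In the row labelled Kidney, grade 3 ends with "Frequent hematuria Reduction in bladder capacity (<150 cc") and grade 4 is "Necrosis/ Contracted bladder (capacity <100 cc) Severe hemorrhagic cystitis". The row labelled Bladder follows directly and carries the same text. The notes below the table give a web address as the source and require the Principal Investigator to verify every grade 3, 4 or 5.

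Elsewhere the Protocol treats the kidney as relevant to radiotherapy. The expected side effects in section 11 include "Chronic renal damage" under RT. Section 9.2 states: "Each kidney is outlined separately if the level of its superior edge overlaps with the level of the inferior extent of the PTV".

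**The concern.** Contracted bladder, bladder capacity and haemorrhagic cystitis describe another organ. A site that follows the table has no criterion by which to give a kidney grade for impaired renal function. A site that sees a late bladder effect finds it described in two rows.

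This table is a working instrument for a secondary outcome in both stages, so the error could reach the data. Late renal morbidity could be missed on the scale meant to capture late radiation effects. A kidney grade that does appear could be a bladder finding under the wrong name. The investigator's verification of grade 3 to 5 entries offers no protection if it is made against the same printed criteria.

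**Working it through.** No sample size, power or event figure is involved, so there is no plan figure to reproduce. The check is a comparison of text.

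**Step 1: compare the two rows cell by cell.** Inputs: the Kidney and Bladder rows of Appendix XII, with content paraphrased here.

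| Grade | Kidney row | Bladder row | Same text? |
|---|---|---|---|
| 0 | none | none | yes |
| 1 | mild epithelial atrophy, minor telangiectasia, microscopic haematuria | the same | yes |
| 2 | moderate urinary frequency, telangiectasia, intermittent visible haematuria | the same | yes |
| 3 | severe frequency and dysuria, severe telangiectasia, frequent haematuria, bladder capacity below 150 cc | the same | yes |
| 4 | necrosis, contracted bladder below 100 cc, severe haemorrhagic cystitis | the same | yes |

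An exact string comparison gives 5 identical cells out of 5.

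**Step 2: look for any renal criterion in the Kidney row.** A search for seven terms (renal, creatinine, urea, albumin, kidney, GFR, clearance) finds none in the grade cells. The Liver row directly above does grade organ function, through liver function tests and albumin. So the table grades function for at least one other organ.

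**Step 3: follow the consequence within this scale.**

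- A patient whose only late effect is impaired renal function, without urinary symptoms or haematuria, meets no Kidney criterion above grade 0.
- A patient with Bladder grade 1 or more meets the same grade in the Kidney row. One event then satisfies two organ rows.

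**Step 4: see what else grades the kidney.**

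- Appendix XI (CTCAE v3.0) has separate items for creatinine, GFR and proteinuria. GFR grade 3, for instance, is "<25% LLN, chronic dialysis not indicated". Section 12.2 applies CTCAE on follow-up too.
- Section 11.1 requires serious adverse reactions to be reported for up to 5 years.
- In section 5.5 the renal, liver and bone profile is marked at screening and weeks 1, 4, 7, 10 and 13, and at no later visit. Sections 5.3 and 5.4 list no renal blood test at week 24 or in follow-up. The CTCAE creatinine and GFR items therefore depend, after week 13, on tests done for clinical reasons.

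The defect is therefore one item of one of two parallel scales. The parallel scale remains usable but has no scheduled laboratory values in the late period.

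**The case against.** The strongest reply is that late renal damage can still be graded in this trial. CTCAE runs alongside through follow-up, and serious reactions are reported for years. That stands. A reader might infer from Appendix XII that late renal damage would be recorded as absent throughout the trial. The documents do not support this; only the RTOG/EORTC kidney item is lost.

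A second reply is that the missing late renal bloods cannot be used to dismiss CTCAE, because a corrected Kidney row that relied on laboratory values would lack the same scheduled tests. That also stands. The assessment schedule limits both scales and is a separate matter.

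Third, a reader might infer that bladder events will be counted twice and that the comparison of late harm between arms will be wrong. The Protocol specifies no analysis of RTOG grades by organ. The only toxicity test in section 12.5 is a chi-squared test on proportions of patients with serious adverse events. The bladder is not among the organs outlined in section 9.2, so few bladder grades are to be expected. Double scoring could follow from the printed table, but nothing shows that it has happened.

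Fourth, cisplatin adds little to the argument. Section 8.4.1 says "Cisplatin produces cumulative nephrotoxicity", but Appendix XII is a radiation schema, cisplatin is given in both arms, and drug toxicity falls to CTCAE. The case rests on the radiotherapy passages, and kidney outlining there is conditional on overlap with the target level.

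Finally, the text was extracted from PDF, and this table breaks across a page at the Oesophagus row. A row repeated in extraction cannot be ruled out. Against that, the two rows are complete, separately labelled and well formed. If the source page had one shared cell for both organs, the defect would be the same.

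**Conclusion.** Wrong as written, minor severity. The Kidney row of Appendix XII repeats the Bladder row in 5 of 5 grade cells and contains no renal criterion. Late renal morbidity therefore cannot be graded on the RTOG/EORTC scale, and a bladder event fits two rows. No primary outcome and no named test is affected.

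The conclusion rests on two assumptions: that the PDF page reads as the extracted text does, and that sites score from this page or from a form that reproduces it. No case report form is shown, so the second is unconfirmed. The correct kidney wording lies in the cited external schema, which is not at hand, and is not asserted here. Section 12.2 calls the scale acute while the appendix it cites is headed late; that is a different point and does not alter this one.

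**What to change.** 1. Compare the Kidney row with the PDF page of the Protocol and with the schema that Appendix XII cites.
2. If the duplication is in the PDF, replace the row with that schema's kidney criteria and issue a corrected page to sites.
3. Check whether the case report form reproduces the row. If it does, or if completed forms were scored from this page, query the kidney grades already returned.

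The cost is one corrected appendix row and, at most, a data query on one item.

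If the PDF turns out to carry distinct kidney criteria, no change is needed.
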